### **Statistical Analysis Plan**

Overall, data from SHARP should assist in answering specific research questions, using independent data sets. As a result, each project proposal will include a detailed statistical analysis plan.

### **Potential Risks and Benefits**

#### *Potential Benefits*

There are no direct benefits to study participants in this research registry. However, information regarding characteristics related to severe asthma will be obtained.

### *Potential Risks*

This research represents a registry documenting severe asthma. The most likely risk posed to study participants would be a breach of confidentiality if someone other than the research team gains access to their data.

### *Mitigation of Risks*

In each participating centre, there will be security measures in place to prevent breach of confidentiality from happening (e.g. locked cabinets, password protected files).

### *Provisions to Protect the Privacy Interest of Registry Participants*

Precautions to protect the privacy of participants in SHARP will be taken according to the EU General Data protection Regulation (GDPR) summarized in a Data Privacy Impact Analysis (DPIA). All precautions will be taken to make sure that only authorized individuals will be accessing study participants research records. The collection of sensitive information about subjects is limited to the amount necessary to achieve the aims of the research registry, so that no unneeded sensitive information is being collected.

## Early Withdrawal of Subjects

### *Investigator Withdrawal of Subjects*

Patients are followed every year in the severe asthma clinic as part of their standard of care. If a patient does not return to the clinic for any regularly scheduled visit, the patient will not be withdrawn but visits will be considered as missing data in the data set. The investigator will have the right to withdraw individual patients if they have evidence that the patient is wilfully giving incorrect information about their asthma. Such withdrawals would have to be discussed and authorised by the national lead and – in case of a strong dispute – mediated by the SHARP CRC.

### *Research subject Request for Withdrawal from Registry*

All study participants can withdraw from the study if they so choose. Patients wishing to withdraw from the research registry will be directed to contact the principal investigator in their study site. From the point of withdrawal, no further data will be collected from the patient or their medical records. However, any data collected up to the point of withdrawal will be maintained for integrity of the research registry. Patients will be made aware of their rights in the informed consent form.

### *Data Collection and Follow-up for Withdrawn Subjects*

Patients who request withdrawal or who are withdrawn by the PI from the registry will have their data maintained in the research database up to the point of withdrawal. This data will be included in subsequent analysis.

## Adverse Event Reporting

The primary purpose of the registry is NOT to systematically document adverse events from treatments, but to follow patients with severe asthma to understand more about the disease. However, since many study participants will be exposed to novel biological treatments for severe asthma, adverse events from these treatments may occur. Therefore, the investigator will seek

information on adverse events at each contact with the study participant, by specific questioning and, as appropriate, by examination. Information on all adverse events should be recorded in the source document and in the SHARP eCRF. All adverse events will be reported to local and national authorities as well as to European Medicines Agency (EMA) and the pharmaceutical industry that produces the biological.

## Ethical Considerations

n/a.

## Sharing of Results with Subjects

Patients will be regularly informed about the results of SHARP studies following practices in different countries.

## Funding Source

SHARP CENTRAL Registry will be supported by funding from the European Respiratory Society (ERS). In the event that ERS funding ends, the participating centers will jointly attempt to obtain further funding from other sources in order to continue the registry.

## Monitoring research progress

For data control there will be continuous evaluation of data for plausibility. There will be additional remote monitoring to check source documents and data entry. This means that original patient records will be compared with the electronic CRF. The investigator should allocate adequate time for these visits and should ensure that the monitor is given direct access to the patient source documents (e.g. hospital files). Between on-site monitoring visits the monitor should regularly check the electronic data for completeness and plausibility of the data. Missing data will be marked.

## Forms and data handling

A complete CRF is attached in the Appendix. The data are entered electronically via internet-based technology. The SHARP CENTRAL Registry web-portal is separated into several parts with different access rules. Any given site investigator in SHARP CENTRAL Registry is allowed to see only data on study participants under the care of the study site to which the site investigator is affiliated. SHARP CRC is allowed to view all data of all centres for plausibility checks, quality control and monitoring. The whole database is saved on a server.

## Modification of the protocol

Any modification of the protocol which may have an impact on the conduct of the study, including study objectives, study design, study participant population, study procedures or significant administrative aspects, will require a formal amendment to the protocol and approval by the ethics committee according to individual country rules.

## Administrative responsibilities

The Investigator is responsible for the adequate medical care of the participant during the study. The Investigator must follow GCP Guidelines and is responsible for the safety and the medical care of the participant.

A contract will be issued to regulate the obligations and rights of the investigator and the responsibilities of SHARP CENTRAL foundation; the contract will be signed between authorized representatives of the respective institutions with which the investigators are affiliated and SHARP CENTRAL foundation, a non-profit charity registered in the Netherlands.

Access to the clinical database is regulated by the policies of SHARP CRC. Researchers interested in obtaining data for further analysis have to submit brief outlines of their severe asthma related research project to the Scientific Review Board of the SHARP CRC. The Scientific Review Board will assess whether the proposed project falls within the subject area to which study participants gave their informed consent and whether the proposal is ethically and scientifically sound. Once a project is approved by the Scientific Review Board, the proposer has to confirm in writing to comply with the data access and publication policy of SHARP and will provide a short abstract on the approved proposal for display at the SHARP web portal. Researchers conducting an approved project will then be granted to use a recoded excerpt of the clinical database for their analyses.

## Publication Plan

The publication policy of SHARP is described in detail in a separate document: “SHARP Publication Process”

## APPENDIX 1: Case Report Form

[to be completed for every patient who is diagnosed with severe asthma]

### Treating physician details

Name:

Hospital:

### Has patient given informed consent for entering the registry

- ☐ Yes  
☐ No

Date of entrance in registry (dd-mm-yyyy):

### Is the patient currently participating in a (randomized) trial in which he/she receives study medication for asthma?

- ☐ Yes  
☐ No

Date of randomization (dd-mm-yyyy):

Year/month of birth (yyyy/mm):

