### *Secondary Objectives*

- To obtain natural history data on a wide spectrum of severe asthma patients
- To expedite identification and recruitment of participants for clinical trials
- To plan for future research studies (observational and interventional trials aimed at better symptom control and improving quality of life).

Research projects should aim to advance scientific knowledge towards optimizing treatment strategies that reduce the burden and costs of severe asthma, improve patients quality of life, and prevent poor outcomes.

The SHARP CENTRAL Registry database containing pseudo-anonymized data will be de-identified and integrated with other anonymized European severe asthma databases via a data integration platform controlled by the SHARP CRC. Data will be used for a variety of different analyses, which may be broadly categorized as either cross-sectional analyses or longitudinal analyses. SHARP CENTRAL Registry places no limit on the sample size to be collected or a timeframe in which the study will be completed. It is intended that data will be collected as long as needed to respond to pending questions defined by the SHARP CRC. The gradual amassing of phenotypical data will result in cumulative increases in statistical power in order to continuously improve the assessment tools that monitor the course of severe asthma and to identify clinical predictors of therapeutic responses, adverse events and patient relevant outcomes.

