### *Enrolment*

Prior to the initial visit, the patient will be consented. Initial baseline demographics of age, gender and ethnicity will be collected from clinic records. Medical history will be collected from clinic records and patient interview. Data from physical examination, diagnostic tests, and current medication use will be taken from clinic records. Patients will be asked to complete 6 questionnaires during clinic visits.

Subsequent yearly appointments: vital signs, height, weight, BMI, pulmonary function tests and current medications will be collected. The study subjects will be asked to complete 6 questionnaires either at the clinic, at home or digitally. All additional registry data (e.g. diagnostic tests) will be collected according to standard of care.

If and when the SHARP CRC develops additional questionnaires or diagnostic tests, these will be added but the patient will have the right to opt out of these and continue with only the original set of questionnaires and diagnostic tests.

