**[To be completed once every year by case-manager]**

Is patient lost to follow-up?

- ☐ yes
  - ☐ Patient passed away
  - ☐ Patient changed email address
  - ☐ Patient withdrew consent
  - ☐ Other \_\_\_\_\_
- ☐ No

Date of examination (dd-mm-yyyy):

Height: \_\_\_\_\_ cm  
 Weight: \_\_\_\_\_ Kg  
 BMI: \_\_\_\_\_ Kg/m^2

Smoking Status:

- ☐ Never Smoker[SEP]
  - ☐ Ex-Smoker (Quit smoking >12 months)
  - ☐ Current Smoker
- Current number of Pack years: \_\_\_\_\_

Has patient ever been admitted to ICU for asthma?

- ☐ Yes
- ☐ No

If yes, total number of ICU admissions:  
Has patient ever been intubated due to asthma?

- ☐ Yes
- ☐ No

If yes, total number of intubations:

Has the patient ever attended rehabilitation

- ☐ Yes
  - How often? \_\_\_\_\_ times
  - Last time \_\_\_\_\_ years ago
- ☐ No[SEP]
- ☐ Unknown

Has the patient ever undergone bronchial thermoplasty?

- ☐ Yes  
Date/year \_\_\_\_\_
- ☐ No[SEP]
- ☐ Unknown

Has spirometry ever been performed (If done multiple times, please report most current result)[SEP]

- ☐ Yes
- ☐ No

If Yes, when was most recent pulmonary function test performed? (dd/mm/yyyy)

If Yes, which values are available?

- ☐ Pre-bronchodilator values
- ☐ Post-bronchodilator values

|          | PRE
BRONCHODILATOR |                | POST
BRONCHODILATOR |                |
|----------|-----------------------|----------------|------------------------|----------------|
| FEV1     | L                     | %
predicted | L                      | %
predicted |
| FVC      | L                     | %
predicted | L                      | %
predicted |
| FEV1/FVC | %                     |                | %                      |                |

Has exhaled NO testing ever been performed?

- ☐ Yes
- ☐ No

If yes, please report date of most recent result:

FeNO \_\_\_\_\_ppb

Has CO diffusion capacity been performed (ever)?

- ☐ Yes
- ☐ No

If yes, please report date of most recent result:

DLCO: \_\_\_\_\_ mmol/min/kPa and \_\_\_\_\_ % predicted

Has bodyplethysmography (body box) ever been performed?

- ☐ Yes
- ☐ No

If yes, please report date of most recent result:

TLC: \_\_\_\_\_ L and \_\_\_\_\_ % predicted

RV: \_\_\_\_\_ L and \_\_\_\_\_ % predicted

Has bronchial provocation testing with methacholine ever been performed ?

- ☐ Yes
- ☐ No

If yes, please report date of most recent result:

- ☐ Positive (BHR demonstrated, FEV1 decline  $\geq 20\%$ )

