- ☐ Yes, because of (very) good response

☐ No, patient is currently not treated with biologics

Does the patient currently use any of the following (non-pulmonary) medications?

- ☐ Nasal corticosteroids[L][SEP]
- ☐ Antihistamines[L][SEP]
- ☐ Bisphosphonates[L][SEP]
- ☐ Calcium suppletion ( $\pm$  vit D)[L][SEP]
- ☐ Proton pump inhibitors[L][SEP]
- ☐ vit K antagonists[L][SEP]
- ☐ NSAIDs[L][SEP]
- ☐ Other

-----  
-----  
-----

[L][SEP]

Has the patient received one of the following asthma add-on treatments  
IN THE PAST?

☐ omalizumab

If Yes, date of last administration (dd/mm/yyyy)

If yes, reason for stopping?

☐ insufficient reduction of systemic steroid dose[L]SEP

☐ Adverse effects[L]SEP

☐ Insufficient improvement of symptoms or exacerbations[L]SEP

☐ Insufficient improvement of lung function

☐ mepolizumab

If Yes, date of last administration (dd/mm/yyyy)

If yes, reason for stopping?

☐ insufficient reduction of systemic steroid dose[L]SEP

☐ Adverse effects[L]SEP

☐ Insufficient improvement of symptoms or exacerbations[L]SEP

☐ Insufficient improvement of lung function

[L]SEP

☐ reslizumab

If Yes, date of last administration (dd/mm/yyyy)

If yes, reason for stopping?

☐ insufficient reduction of systemic steroid dose[L]SEP

☐ Adverse effects[L]SEP

☐ Insufficient improvement of symptoms or exacerbations[L]SEP

☐ Insufficient improvement of lung function

[L]SEP

☐ benralizumab

If Yes, date of last administration (dd/mm/yyyy)

If yes, reason for stopping?

☐ insufficient reduction of systemic steroid dose[L]SEP

☐ Adverse effects[L]SEP

☐ Insufficient improvement of symptoms or exacerbations[L]SEP

☐ Insufficient improvement of lung function

[L]SEP

☐ dupilumab

If Yes, date of last administration (dd/mm/yyyy)

If yes, reason for stopping?

☐ insufficient reduction of systemic steroid dose[L]SEP

☐ Adverse effects[L]SEP

☐ Insufficient improvement of symptoms or exacerbations[L]SEP

- ☐ Insufficient improvement of lung function

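### The protocol disagrees with itself on whether trial participation is asked again after entry, and the form cannot reliably flag time on blinded study medication

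*Protocol*

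**What the plan says.** Appendix 1 opens with the instruction "to be completed for every patient who is diagnosed with severe asthma", which gives no frequency. The items that follow are consent, entry date, trial participation, birth month, gender, ethnicity and age at diagnosis. The trial item reads "Is the patient currently participating in a (randomized) trial in which he/she receives study medication for asthma" and takes a yes or no plus a date of randomization. It has no field for the end of study medication, the type of drug or blinding.

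Two blocks with an annual label come after these items. One is for the patient and holds the six questionnaires. The other is headed "To be completed once every year by case-manager" and holds the clinical, medication and biologic items. Neither contains a trial item. The biologic question in the second block offers five named drugs or "No, patient is currently not treated with biologics".

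The text describes follow-up content in two ways. Study design, in the overview, says that annual visits collect the same data as the baseline visit. Enrolment, under Registry Procedures, says "Subsequent yearly appointments: vital signs, height, weight, BMI, pulmonary function tests and current medications will be collected", then adds the questionnaires and other registry data according to standard of care.

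Secondary Objectives include "To expedite identification and recruitment of participants for clinical trials". Consent Procedures provide a separate consent level for later invitations to further research.

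**The concern.** The registry intends some of its participants to enter trials after enrolment. Nothing in the exclusion criteria, the withdrawal rules or Registry Duration removes them when they do, so their annual records continue. For those records to be usable, the form must show which intervals were spent on study medication.

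Response to treatment is part of the primary objective, and natural history is a secondary one. An interval on blinded active drug that is recorded as no biologic puts treated time into an untreated category. An interval on placebo is coded correctly for drug exposure, but it is still not plain routine care if nobody can see that it belonged to a trial. The Statistical Analysis Plan section leaves the analysis to each project, and a project plan can only set aside or adjust for intervals that it can identify. The gap is therefore in the collection instrument printed in this protocol, not in an analysis plan.

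**Working it through.** The protocol states no figure on this point, so the check sets the passages side by side.

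**1. Is the trial item repeated after entry?**

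| Source | What it implies |
|---|---|
| Study design (overview) | Yes, if the rule on identical follow-up data is read literally |
| Appendix 1, block labels | Not shown as annual: the item precedes both annual blocks and neither repeats it |
| Appendix 1, opening instruction | Silent on frequency |
| Enrolment | Trial participation not named in the follow-up list |

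These do not agree, and sites could reasonably act differently.

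**2. If it is repeated every year, does it capture the exposure?** The item asks about the present and records only a start date. Suppose a patient is randomized after one annual visit and takes the last study dose before the next. The true answer is no at both visits, so the interval is lost even with perfect completion.

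**3. What can be entered in the annual biologic item for a trial participant?**

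| Situation at the visit | Available answer |
|---|---|
| Open-label use of a listed biologic | The named drug, correct |
| Placebo, or a trial of a non-biologic drug, with no other biologic | No, correct for this field |
| Active arm of a blinded biologic trial | No answer known to be correct; No or blank is likely |

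Misclassification in this field is confined to the last row. The missing trial flag affects all three.

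**4. Can the size be derived?** Let f be the share of records coded as no biologic that belong to patients in a blinded biologic trial, and r the share of those allocated to active drug. The share of that group actually on active drug is f × r. If trial drug and registry biologics had equal effect, a treated-versus-untreated difference would keep the fraction 1 − f × r. The protocol gives neither f nor r. With purely assumed values, f = 0.02 and r = 1/2 give 0.02 × 0.5 = 1.0%, and f = 0.20 and r = 2/3 give 0.20 × 0.667 = 13.3%. A range of more than tenfold reflects only the assumptions, so it is not an estimate for this registry.

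**The case against.** The strongest reply is that the overview's rule on identical follow-up data governs, so the trial item is asked every year. The block that holds it is nowhere labelled as once only, and the printed form does not show how the electronic forms repeat. The Enrolment list is weak evidence the other way. It also leaves out smoking, ICU admissions, comorbidities and adherence, all of which are in the annual block, and it refers to additional registry data. This stands: a reader might infer from the layout that trial participation is asked once only, and the documents do not say so. They support a contradiction that needs resolving. The missing end date and the missing answer for blinded drug remain under either reading.

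A reader might also infer that later trial entrants are systematically coded as not treated with biologics. No completion rule says this. The field may be left blank, and the code is right for placebo and for non-biologic trials. The recruitment objective refers to clinical trials in general, not to blinded biologic trials.

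Nor do the documents show that the loss is permanent. The registry draws on medical files, source records are checked against the database, and the list of past treatments takes a last administration date for each named biologic and has an open line for others. A drug unblinded later could be entered there. These routes depend on someone knowing to look, because nothing prompts for a trial. Analysts work on anonymized merged data or a recoded excerpt, so they would find it hard to go back to the files themselves.

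**Conclusion.** The point holds as a defect in data capture. The overview, the Enrolment section and the block labels in Appendix 1 disagree on whether trial participation is asked after entry. Independently of that, the item misses trials that start and end between annual visits, and the biologic question has no correct answer for a patient on blinded active drug. Since the registry aims to help recruit its participants into trials, there is a real risk of unflagged trial intervals in natural-history and treatment-response data.

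The size is unknown. It depends on how many participants enter blinded biologic trials, on the allocation, and on how sites fill in the form, and the documents give none of these. The protocol also prespecifies no treated-versus-untreated comparison, so any statement about a diluted effect is hypothetical. A demonstrated distortion of results is not supported. That analysts cannot reliably identify these intervals is supported.

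**What to change.** - Place the trial item in the annual case-manager block, and word it to cover the time since the last registry visit. Record the date of randomization and the date of last study medication.
- Add an answer for blinded study medication to the question on current biologic therapy.
- Reconcile Study design and Enrolment with the block labels in Appendix 1, so that it is clear which items are asked once and which every year.
- Carry a trial-interval flag in the analysis dataset, and leave its handling to each project's plan. A blanket exclusion is better not fixed here, because it would remove a selected group of trial-eligible patients from a registry that seeks a wide spectrum of disease.

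The cost is a few extra fields per annual visit and some edited text. Whether this needs a formal amendment follows from the protocol's own section on modifications.

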### Gender

- ☐ Male  
☐ Female

### Ethnic background

- ☐ Caucasian  
☐ Non-Caucasian  
☐ Asian

Age at which doctor first diagnosed asthma \_\_\_\_\_ yr

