## Objectives

### *Primary Objective*

SHARP CENTRAL Registry is the central registry of ERS SHARP CRC and primarily designed to collect prospective data on the phenotypical characteristics of patients with severe asthma, treatment strategies and patient responses to treatment, burden of severe asthma across Europe at baseline and during follow-up.

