### **Registry Data Points**

Initial baseline demographics of age, gender and ethnicity will be collected from clinic records. Medical history (age of asthma onset, hospital admissions, ICU admissions, co-morbidities) will be collected from clinic records and patient interview.

Data from physical examination (height, length, blood tests, sputum tests, skin prick tests, pulmonary function test, Chest X-ray, Chest CT, DEXA scan, bronchoscopy, medication use will be taken from clinic records.

Questionnaires: Asthma control questionnaire (ACQ) (17), Severe asthma questionnaire (SAQ) (22).

Additional Questionnaires that are set up for the project “SAQ-Burden of Asthma” and that could potentially be added for future SHARP studies:

Asthma quality of life questionnaire (AQLQ) (18), Work productivity and activity impairment (WPAI) (19), Health care utilization (HCI) (20), Checklist individual strength (CIS) (21).

The questionnaires will be completed by the patient either at the clinic, at home or by a e-device at least once a year.

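### Two case report form items, ethnicity and smoking status, cannot be coded consistently as written: the ethnicity boxes overlap and a recent quitter has no smoking box

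*Protocol*

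**What the plan says.** **Ethnicity.** Under Registry Data Points the protocol states: "Initial baseline demographics of age, gender and ethnicity will be collected from clinic records". The Ethnic background item in Appendix 1 provides three boxes: Caucasian, "Non-Caucasian" and Asian. It has no instruction on which takes precedence, no definition, and no box for unknown or not recorded. Elsewhere the same form does offer an unknown box, for example for rehabilitation, bronchial thermoplasty and the listed co-morbidities.

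**Smoking.** The yearly case-manager section has three boxes: never smoker, "Ex-Smoker (Quit smoking >12 months" (the bracket closes there) and current smoker. It also asks for pack years, but not for a quit date.

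**Lung function.** The block that begins "Has spirometry ever been performed" takes FEV1 and FVC in litres and as % predicted. Later items take DLCO, TLC and RV in absolute units and as % predicted. No reference equation is named, and no field records which one was used. The Enrolment section gives the source: "Data from physical examination, diagnostic tests, and current medication use will be taken from clinic records". The form also collects height, sex, birth date ("Year/month of birth (yyyy/mm") and test date ("If Yes, when was most recent pulmonary function test performed? (dd/mm/yyyy").

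**Use.** The Primary Objective covers phenotypic characteristics, treatment and "burden of severe asthma across Europe at baseline and during follow-up". The country databases are merged into one file for analysis.

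**The concern.** A coded item works only if each patient fits exactly one category. Ethnicity fails because one box lies inside another, and smoking fails because one group of patients has no box. In both cases, different entries for identical patients can each be defended from the form.

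The planned quality control would not settle the ethnicity problem. The Data Quality section relies on coded answers, range checks and comparison with the patient file, and for an Asian patient either entry agrees with the file. Each country has its own database, so coding habits could differ systematically by country and then enter the merged file.

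What is at stake is the accuracy of two descriptive covariates in an open-ended registry whose records will feed many later projects. A project's analysis plan cannot separate categories that were never distinguished at entry. That makes this a matter of data capture and not of deferred analysis detail.

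**Working it through.** **1. Are the ethnicity boxes exclusive and exhaustive?**
- A Caucasian patient fits one box.
- An Asian patient fits two, Asian and the broader box.
- Any other patient fits only the broader box.
- A patient whose ethnicity is not in the records fits none.

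**2. Which contrast is affected?** Let *f* be the share of Asian patients ticked in the broader box, and *r* the ratio of Asian to other non-Caucasian patients. The Asian box then holds only Asian patients, and the broader box holds *f·r* Asian patients for every 1 other. If miscoding is unrelated to the outcome,

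observed difference / true difference = 1 / (1 + *f·r*).

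The documents give neither *f* nor *r*. On assumed values:

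| | *f* = 0.25 | *f* = 0.50 | *f* = 0.75 |
|---|---|---|---|
| *r* = 0.5 | 0.89 | 0.80 | 0.73 |
| *r* = 1 | 0.80 | 0.67 | 0.57 |
| *r* = 2 | 0.67 | 0.50 | 0.40 |

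For example, 1 / (1 + 0.5 × 1) = 0.67. With exclusive boxes *f* = 0 and the factor is 1. Caucasian versus all others does not depend on *f*, because both remaining boxes fall on the same side.

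**3. Is smoking status exhaustive?** Someone who stopped, say, six months ago is not a never smoker, is excluded from the ex-smoker box by its 12-month limit, and no longer smokes. No box is correct. Pack years do not identify such a patient, and no quit date is collected. The documents give no share of recent quitters, so no size can be attached.

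**4. Is % predicted recoverable?** If another site's reference value is higher by a fraction *d*, the same litres are reported as P / (1 + *d*). An 80% predicted becomes 80/1.02 = 78.4, 80/1.05 = 76.2 or 80/1.10 = 72.7 for an assumed *d* of 2%, 5% or 10%. The litres do not change. Age at test follows from birth month and test date, and sex and height are on the form, so one equation can be applied to all countries and *d* becomes 0.

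The protocol states no sample size, power or alpha that bears on this point, so there is no planned figure to reproduce.

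**The case against.** The strongest reply is that little in the plan depends on these items. No objective names an ethnic comparison, the one contrast that is blurred is not planned, and pooling two boxes restores a clean Caucasian versus other split. All of this stands, and it limits the weight of the point.

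The missing unknown option is partly covered, because the section on monitoring research progress says missing data will be marked. A blank, however, does not separate ethnicity that is not in the file from an item that was overlooked.

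A reader might infer three stronger things that the documents do not support:

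- *That ethnic and cross-country comparisons are in fact misclassified.* The form shows only that they can be. Site coding practice is not described, and items such as eosinophils, FeNO or ACQ are untouched by the overlap.
- *That the ethnicity coding is beyond repair once data are anonymised and merged.* The merged file is an export from pseudonymised country databases, and the protocol provides for comparing patient files with the eCRF. Correction upstream and re-export look feasible. They must be reconciled with the rule that identifying information is opened only in medical urgency.
- *That unrecorded reference equations corrupt cross-country lung function.* This is a question of comparability, not misclassification. The absolute values are collected, each project brings its own analysis plan, and nothing says the site-reported percentage will be the analysed variable.

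**Conclusion.** The point holds as a modest data-capture defect in two items. The ethnicity boxes overlap and lack an unknown option, and smoking status leaves out patients who stopped within the past 12 months. Both faults are plain from the form and need no assumption.

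Their effect is narrow: possible dilution of Asian versus other non-Caucasian comparisons, and inconsistent coding of recent quitters. The factors of 0.40 to 0.89 are illustrations on assumed inputs, not estimates for this registry, and they presume that miscoding is unrelated to the outcome. No sample size or power figure changes.

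The % predicted issue is secondary and can be resolved at analysis. One qualification applies: an equation that takes ethnicity as an input would inherit the overlap in the ethnicity item.

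**What to change.** 1. **Ethnicity.** Make the options mutually exclusive and exhaustive. The minimum is Caucasian, Asian, other non-Caucasian, and unknown / not recorded. A finer list is a matter of choice.
2. **Smoking.** Either add an option for patients who stopped within the past 12 months, or remove the 12-month limit from the ex-smoker box.
3. **Spirometry (secondary).** For cross-country comparisons, derive % predicted centrally with one named equation from litres, height, sex and age at test. Keep the site value as a check. This needs no new data and can wait for the analysis.

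The cost is an eCRF option-list change, handled under the section on modification of the protocol if it is judged to fall there, and a short derivation program for the third item. The main burden is a query to sites on records already coded "Non-Caucasian", within the protocol's limits on access to identifying information. Enrolment is ongoing, so an early change means fewer records to query.
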